# Study Objectives

The primary objective of this Neonatal Foot Length (Neofoot) study is to determine the diagnostic accuracy of foot length measurement to predict preterm birth and low birth weight in rural PNG.

Secondary objectives are to:

1. Compare foot length, MUAC and head circumference as predictors of preterm birth and low birth weight
2. Validate a specific foot length cut-off or derive a new cut-off appropriate for PNG
3. Assess the feasibility of using foot length as a measure for preterm birth and low birth weight in the community and health centre by community reporters/volunteers and health centre staff.
4. Determine associations between foot length at birth, physical growth and development of the infant at 6 months, according to study arm.

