### Post-natal 72 hours and 6 month assessments

At the first post-natal (72 hours) assessment, anthropometric measurements in addition to those collected for WANTAIM will be carried out, either at the health facility or at home. At this time, a follow-up visit will be planned for 6 months later, to take place at a health centre. Table 1 shows the measurements that will be collected at each assessment.

Foot length will be measured using a stiff clear plastic ruler. The right foot will be measured from the heel to the tip of the big toe.18

As part of the 72-hour post-natal assessment, the mother or care giver will also be given post-natal health information about immediate care of her newborn infant. The handheld baby book will be used as a guide to discuss essential care of the baby (cord care, keeping the baby warm, regular breast feeding, immunisation and well clinic schedules at 1 month, 2 months, 3 months, 4 months, 5 months and 6 months), recognising danger signs in newborn and infants and actions to take in the event of these.

The 6-month follow-up visit will be conducted at a health centre or at home if the mother/care giver does not attend the clinic visit. The research registrar will be responsible for assessing the baby and collecting the anthropometric and development data (Table 1) and recording it in the study-specific CRF. Information about growth assessments using World Health Organization growth charts, immunisations, illnesses and hospital admissions in the period between the two visits will be obtained from discussion with the mother/care giver and from the baby book and recorded in the study specific CRF. If the registrar is concerned about a particular aspect of the infant’s development, or if the infant is unwell (including undernourished), the paediatric registrar will follow routine procedures for referring that infant for paediatric review either as an outpatient or an emergency, as the situation warrants. In addition, if the visit takes place in the home, the mother will be advised to attend the child health clinic to update immunisations, as required.

Table 1: Description of procedures at Neofoot study assessments within 72 hours and at 6 months

| **Procedures** | **Description or method** | **Person responsible** | **Neofoot enrolment** |
| --- | --- | --- | --- |
| Eligibility | Assess whether participant satisfies criteria to join the study | Researcher | X |

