## Statistical analysis

I will examine the distributions of each variable. I will describe continuous variables using histograms, mean and standard deviation, and median and interquartile range. I will describe frequencies of categorical variables as percentages. I will conduct a descriptive analysis to examine associations with preterm delivery and low birth weight, including social and demographic factors (collected during WANTAIM assessments) and achievement of developmental milestones at 6 months and between study arms and achievement of developmental milestones at 6 months. I will assess the correlation between the gestational age at birth (measured by USS) and birthweight (measured using digital scales) and anthropometric measures (foot length, head circumference, MUAC) using Spearman’s rank correlation coefficient.

I will calculate diagnostic performance of foot length as: a) sensitivity (proportion of newborns correctly identified as preterm, low birthweight or very low birth weight); and b) specificity (proportion of newborns correctly identified as not preterm or not low birth weight) for 1mm increments in foot length. I will also calculate sensitivity and specificity for head circumference (1.0cm increments) and MUAC (1mm increments).8

To assess the diagnostic performance of each anthropometric measure as a predictor of preterm birth, low birth weight and very low birth weight, I will construct receiver operating characteristic (ROC) curves.24 The ROC curve is a graphical plot of sensitivity (vertical axis) against 1 minus specificity (horizontal axis) for each increment in measurement of the anthropometric measure. The best cut-off for each measure is the value at which the sensitivity and specificity are highest. I will then calculate the area under the curve (AUC, with 95% confidence intervals) as a proportion of the total area. The closer the AUC value is to one, the better the predictive value.

I will provide the best cut-off for the prediction of preterm birth, low birth weight and very low birth weight using foot length, head circumference and MUAC. I will recommend the most appropriate and simple measure based on my findings.

I will use linear regression to examine associations between the foot length at birth and achievement of developmental milestones, with multivariable models to control for potential confounding.

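### Comparing the three measures is an objective, but the planned analysis never estimates a difference between them and so leaves the same-baby pairing unused

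*Protocol*

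**What the plan says.** Under Study Objectives, the first secondary objective is to "Compare foot length, MUAC and head circumference as predictors of preterm birth and low birth weight".

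The Statistical analysis section then describes results one measure at a time:

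- Spearman correlations of gestational age and birth weight with each measure.
- Sensitivity and specificity by increment: 1 mm for foot length and MUAC, 1.0 cm for head circumference.
- ROC curves "To assess the diagnostic performance of each anthropometric measure as a predictor of preterm birth, low birth weight and very low birth weight".
- A best cut-off for each measure and outcome.
- The area under each curve: "I will then calculate the area under the curve (AUC, with 95% confidence intervals) as a proportion of the total area".

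The AUC is read by its value: "The closer the AUC value is to one, the better the predictive value". The recommendation follows directly: "I will recommend the most appropriate and simple measure based on my findings".

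The section names no difference between measures, no paired analysis, and no link from the accuracy results to the recommendation.

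That the measures come from the same babies is an inference. There is one cohort, and the section on the 72-hour and 6-month assessments says "At the first post-natal (72 hours) assessment, anthropometric measurements in addition to those collected for WANTAIM will be carried out". Table 1, which would settle the point, is incomplete in the text at hand.

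**The concern.** A comparison needs an estimated contrast. Three AUCs with three separate intervals describe each measure but do not say how much better one is than another, or how certain that is. Two measures taken on the same baby tend to err together, so their AUC estimates are positively correlated. The interval for their difference is therefore narrower than the separate intervals suggest, and that information is lost if no paired difference is computed. Nor do the best cut-offs fill the gap: sensitivities read at separately chosen cut-offs generally sit at different specificities and cannot be compared directly.

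At stake is the study's practical output, the measure recommended for community use. Without a contrast and its interval, a reader cannot tell a demonstrated accuracy advantage from sampling noise, or a choice made on accuracy from one made on simplicity.

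**Working it through.** **Inputs from the Protocol (Sample size).** 400 invited × 0.95 × 0.90 = 342 neonates, which reproduces the stated figure. The Protocol gives no precision or power figure for comparing measures; its ±4 to 5% concerns sensitivity.

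**Assumptions not in the Protocol.** Case share 10–20% (342 × 0.10 = 34.2 and 342 × 0.20 = 68.4, so 34–68 cases), within-class correlation between measures 0.3–0.8, and true AUCs as shown. Measures were simulated as correlated binormal, with DeLong variances.

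**Formula.** Paired: Var(A1 − A2) = Var(A1) + Var(A2) − 2Cov(A1, A2). Ignoring pairing drops the covariance term.

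**Size of the covariance, one cell.** For 51 cases, correlation 0.5 and both AUCs 0.85, the standard errors are 0.030 paired and 0.040 unpaired. The variances are 0.00090 and 0.00160, so 2Cov = 0.00070. Each AUC has variance of about 0.00080, so the correlation between the two AUC estimates is 0.00035 / 0.00080 = 0.44.

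**True AUC 0.85 versus 0.80** (1,000 runs per row; a third measure is also at 0.80). The last two columns come from runs with all AUCs equal to 0.85.

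| Cases | Correlation | SE paired | SE unpaired | Detected, paired | Detected, unpaired | Better measure ranks first | False positive, paired | False positive, unpaired |
|---|---|---|---|---|---|---|---|---|
| 51 | 0.3 | 0.0377 | 0.0436 | 27.8% | 18.6% | 84.4% | 6.2% | 2.2% |
| 51 | 0.5 | 0.0325 | 0.0434 | 31.8% | 12.8% | 89.0% | 4.4% | 0.7% |
| 51 | 0.7 | 0.0260 | 0.0435 | 47.5% | 8.0% | 94.8% | 5.5% | 0.2% |
| 68 | 0.3 | 0.0336 | 0.0388 | 30.2% | 20.4% | 88.8% | 5.7% | 2.9% |
| 68 | 0.5 | 0.0292 | 0.0389 | 37.6% | 17.5% | 91.0% | 4.5% | 0.7% |
| 68 | 0.7 | 0.0233 | 0.0391 | 60.0% | 14.4% | 97.4% | 5.7% | 0.1% |

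The paired contrast keeps close to its nominal 5% error. The unpaired one falls below it, and further as the correlation rises.

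**True AUC 0.87 versus 0.77** (34–68 cases, correlation 0.3–0.8). The standard error is about 0.020–0.045 paired and 0.039–0.052 unpaired. Detection is about 62–100% paired and 46–89% unpaired. A normal approximation at the two ends agrees:

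- 34 cases, correlation 0.3. Paired: 0.10 / 0.045 − 1.96 = 0.26, so about 60%. Unpaired threshold 1.96 × 0.052 = 0.102; (0.10 − 0.102) / 0.045 = −0.04, so about 48%.
- 68 cases, correlation 0.8. Paired: 0.10 / 0.020 − 1.96 = 3.04, so over 99%. Unpaired threshold 1.96 × 0.039 = 0.076; (0.10 − 0.076) / 0.020 = 1.2, so about 88%.

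**Small gaps.** The paired 95% half-width runs from 1.96 × 0.020 = 0.039 to 1.96 × 0.045 = 0.088, so an observed gap of 0.03 lies inside it throughout. Three measures with equal AUCs of 0.85 show a mean top-to-bottom gap of 0.026–0.050 by chance (correlation 0.3–0.7). With true AUCs of 0.83, 0.80 and 0.80 and 34 cases, a wrong measure has the largest AUC in 21–36% of studies (correlation 0.5–0.8).

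**The case against.** **An overlap rule.** A reader might infer that the measures will be judged by whether their separate intervals overlap, which would be very conservative. The Protocol does not say so. It names no method of comparison and no unpaired test, so pairing is left unused rather than expressly discarded. Detection rates under a non-overlap rule would measure something the plan does not contain, and none is relied on here.

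**A choice left to chance.** A reader might also infer that the recommended measure is simply whichever AUC happens to be largest. That is not supported either. Correlations, sensitivity and specificity are also reported, and simplicity is a stated criterion. Even on AUC alone, a measure with a true lead of 0.05 over both others ranks first in 77–97% of runs (34–68 cases, correlation 0.3–0.7), and one with a lead of 0.10 in 99–100%.

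**Detail for a statistical analysis plan.** The choice between DeLong and the bootstrap, or the definition of the complete-case set, can wait for a plan not shown here. This stands for the technique. It does not fully answer the point, because the Protocol's own section fixes increments, cut-offs, intervals and the recommendation step, and the contrast its objective calls for is absent from that sequence.

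**Limited gain.** This stands in part. At a true gap of 0.03 with 34 cases, the paired contrast has only about 12–20% power (correlation 0.5–0.8), so it would seldom identify the better measure. Its value there is to show that the question is unresolved. The objective is secondary, and the primary objective is unaffected.

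**Conclusion.** The point holds in a limited form. Followed as written, the analysis never estimates the difference that secondary objective 1 asks about, and the recommendation cannot be traced either to a demonstrated accuracy advantage or to simplicity. This matters most when the AUCs lie within about 0.03 of each other.

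Under the stated assumptions, using the pairing lowers the standard error of an AUC difference from about 0.039–0.052 to 0.020–0.045, and raises detection of 0.87 versus 0.77 from about 46–89% to 62–100%. The direction follows from any positive correlation between the AUC estimates. The size depends on case share, correlation and true AUCs, none of which the Protocol gives, and on all three measures being taken on the same babies. This is an inexpensive improvement to a secondary analysis and does not invalidate the study.

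**What to change.** In the Statistical analysis section, after the AUC sentence, add:

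- The paired difference in AUC (for example DeLong) with its 95% confidence interval, for foot length against MUAC and foot length against head circumference, for preterm birth and for low birth weight, in babies with all three measures. That is 2 contrasts × 2 outcomes = 4 intervals, to be read as estimates.
- Optionally, the paired difference in sensitivity at a common specificity.
- A statement, alongside the recommendation, of whether it rests on a demonstrated accuracy difference or on simplicity. A rigid rule that a measure counts as better only if the interval excludes zero is not required.

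A related caution: compute each AUC from the recorded values. If the head circumference curve is built on the 1.0 cm grid, an AUC of 0.85 falls to about 0.83–0.845 (assumed SD 1–2 cm), which would bias the difference against that measure.

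The cost is a few sentences and a standard ROC comparison command. No new data or visits are needed.

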# Background

Every year over 4 million babies die in the first four weeks of life (the neonatal period) globally. Of these deaths, three million occur in the first seven days (early neonatal period).1-3 Ninety-eight percent of all neonatal deaths occur in developing countries where the risk of neonatal death is six times higher than in developed countries.1 Neonatal death rates are high in remote rural areas, where access to maternal and newborn health services, including skilled health professionals, is limited.4 The most common causes of early neonatal deaths are complications of pregnancy or childbirth, preterm birth, congenital malformations and infections or neonatal sepsis.1 Small for age or low birth weight infants are at higher risk of dying from infections than normal birth weight or appropriate for age infants.5 Preterm birth (babies born at less than 37 completed weeks gestation) and low birth weight (infants born weighing less than 2500g; <1500g birthweight is defined as very low birth weight) are two main factors that significantly contribute to neonatal mortality.1 Preterm birth is associated with delayed development, but evidence about the outcomes of those surviving the neonatal period is scarce.6 A systematic review that found 197 studies measuring outcomes of preterm birth in low and middle income countries found that only 16% were performed in community settings, 19% assessed developmental outcomes, none was done in the Pacific Region, and only 11% fulfilled criteria for high quality.6

Simple, affordable tools to assess gestational age and birth weight would help to identify newborns that may need referral for further assessment or urgent interventions. There are several methods for assessing gestational age during pregnancy, and this includes last menstrual period, fundal height, or ultrasound scan (USS) before 22 weeks of gestation. Neonatal gestational age can be estimated from either the Dubowitz (22 clinical factors)7 or Ballard score (12 clinical factors).8 However, a major challenge, particularly in resource-limited settings, is that for such diagnostic tools, skilled health workers, or complex equipment, or both, are usually needed to assess gestational age accurately.8

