## Eligibility criteria

Women enrolled in the two WANTAIM sites will be eligible if they have complete data on USS assessment of gestational age and have a post-natal visit completed within 72 hours of birth. Women whose baby died in the perinatal period, or who have very sick babies or babies with congenital abnormalities that restrict team from collecting outcomes within 72 hours of birth, or who will be moving out of the catchment area within the next 6 months, will be excluded. Locator information for eligible participants, collected at WANTAIM enrolment will be updated.

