## Sample size

The maximum sample size will be determined by the number of women in WANTAIM who deliver during the study period. The required sample size is determined by the required precision around the estimates of sensitivity, the primary outcome. Based on projections of trial enrolment at the study clinics, an estimated 400 women will be invited to participate. If 95% have a 72-hour post-natal visit and 90% of mothers agree to foot length measurement and follow up, there will be 342 neonates. If sensitivity is 70-90%, 95% confidence intervals will be +/- 4 to 5%, which is an acceptable level of precision. If 80% of these infants are followed up at 6 months, we will have repeated anthropometric and physical development measurements on 274 infants. This sample size also ample statistical power for secondary outcomes, such as differences in the mean foot length at birth between infants who have or have not reached one or more developmental milestones. Assessment of the reliability of foot length measurements by community reporters will be measured using the kappa statistic (κ). Based on a published study,18 if agreement is fair between two raters’ measurements of a foot length <8cm, 143 pairs of observations are needed for an estimate of κ=0.4 and its 95% confidence interval. We will therefore enrol 150 consecutive babies for this assessment.

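### The protocol commits to a best cut-off for very low birth weight, an outcome outside its objectives, and under plausible prevalences 342 neonates would give too few cases to derive one.

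*Protocol*

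**What the plan says.** The Background of the protocol sets the threshold: "<1500g birthweight is defined as very low birth weight". The Statistical analysis section then treats this outcome on the same footing as preterm birth and low birth weight. ROC curves are planned for each anthropometric measure as a "predictor of preterm birth, low birth weight and very low birth weight, I will construct receiver operating characteristic (ROC) curves", and the commitment follows: "I will provide the best cut-off for the prediction of preterm birth, low birth weight and very low birth weight", for foot length, head circumference and MUAC. The selection rule is "The best cut-off for each measure is the value at which the sensitivity and specificity are highest". No minimum number of cases is attached to it, and no descriptive alternative is given for a rare outcome.

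The Sample size section starts from "an estimated 400 women will be invited to participate" and, after allowing for attendance and consent, concludes that "there will be 342 neonates". It gives no expected number of preterm, low birth weight or very low birth weight infants.

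The Eligibility criteria exclude "Women whose baby died in the perinatal period, or who have very sick babies or babies with congenital abnormalities". The sentence goes on to limit the sickness and abnormality exclusions to cases where outcomes cannot be collected within 72 hours of birth. The Study Objectives name preterm birth and low birth weight only.

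**The concern.** The precision of sensitivity depends on the number of affected infants, not on the number of infants measured. Birth weight under 1500 g is the rarest of the three target conditions, because it is a subset of low birth weight, and the exclusions probably fall hardest on the smallest babies. If only a few cases remain, the chosen threshold follows the measurements of one or two infants. The same infants then supply both the cut-off and the estimate of how well it works, so that estimate is too favourable.

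The published output would be three cut-offs for the highest-risk group, one per measure, with apparent accuracy that new data would be unlikely to reproduce. Correcting the general precision statement in the Sample size section would not prevent this, because the commitment stands separately in the Statistical analysis section.

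**Working it through.** **Inputs.** From the Sample size section: 400 invited, 95% attendance, 90% consent, anticipated sensitivity 70-90%, precision ±4 to 5%. From the Background: threshold 1500 g. The prevalence of very low birth weight is not in the protocol. It is assumed here and varied.

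**Step 1, the plan's own figures.** 400 × 0.95 × 0.90 = 342, as stated. No deduction is made for the eligibility exclusions. The stated precision is approximated only with all 342 neonates as the denominator of sensitivity: 1.96 × √(s(1−s)/342) gives ±4.9 points at s = 70%, ±4.2 at 80% and ±3.2 at 90%. It therefore says nothing about an outcome with few cases.

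**Step 2, expected cases** = 342 × assumed prevalence, with the binomial 2.5-97.5% range:

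| Assumed prevalence | Expected cases | Range |
|---|---|---|
| 0.5% | 1.7 | 0-5 |
| 1% | 3.4 | 0-7 |
| 1.5% | 5.1 | 1-10 |
| 2% | 6.8 | 2-12 |
| 3% | 10.3 | 5-17 |

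The probability of no case at all, (1 − p)^342, is 18% at 0.5% and 3% at 1%.

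**Step 3, exact interval when every case is detected.** With n of n detected, the two-sided 95% Clopper-Pearson lower limit is 0.025^(1/n):

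- n = 2: 15.8%
- n = 3: 29.2%
- n = 5: 47.8%
- n = 7: 59.0%
- n = 10: 69.2%

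The upper limit is 100% each time. With one or two cases missed the intervals are 28-99% for 4 of 5 and 44-97% for 8 of 10.

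**Step 4, sensitivity to the assumption.** At 5% prevalence there would be 342 × 0.05 = 17.1 cases. The approximate half-width 1.96 × √(s(1−s)/17.1) is then 14 points at s = 90% and 22 points at s = 70%. A half-width of 5 points needs 1.96² × s(1−s)/0.05² cases: about 138 at 90% and 323 at 70%, or 40% and 94% of the 342.

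**Step 5, effect of choosing the cut-off on the same data.** The stated rule was simulated with 342 neonates, normal foot lengths (mean 77 mm in non-cases, SD 4 mm in both groups), 1 mm increments, and the cut-off maximising sensitivity plus specificity. These settings are assumptions. At a true AUC of 0.95:

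| Cases | Apparent sensitivity | True sensitivity of chosen cut-off | Central 95% of chosen cut-off |
|---|---|---|---|
| 3 | 98% | 75% | 65-75 mm |
| 5 | 95% | 81% | 67-75 mm |
| 7 | 94% | 82% | 68-74 mm |

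Over assumed AUCs of 0.90 to 0.98 and 3 to 7 cases, the optimism is roughly 11 to 22 points and the chance spread of the cut-off about 6 to 11 mm. For scale, the Background gives published cut-offs for preterm birth or low birth weight from 6.8 to 8.0 cm, a span of 12 mm.

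**The case against.** The strongest reply is that the scarcity of cases is not a fact in the protocol. No prevalence is given, so any count is conditional. This stands, and the counts above are labelled as assumptions. The conclusion does not depend on one value, since even 5% leaves half-widths of 14 to 22 points.

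Four stronger readings are tempting, and the document does not support them.

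- A reader might take 342 to be the number left after the exclusions. It reflects attendance and consent only.
- A reader might think that all very sick babies are excluded. They are excluded only where outcomes cannot be collected within 72 hours. A disproportionate loss of the smallest infants is likely, but nothing in the protocol quantifies it.
- A reader might say that apparent sensitivity is 100% by construction. The rule weighs specificity as well, so a case with a long foot can be given up. In simulation at AUC 0.95, all cases are captured in about 98% of samples with 2 cases, but in 79% with 5 and 63% with 7. At AUC 0.90 the figures are 94%, 62% and 47%. Optimism and instability remain, but full capture is not guaranteed.
- A reader might infer that a very low birth weight cut-off will be recommended for field use. The protocol says that cut-offs will be provided and that a measure will be recommended. Its feasibility objective concerns preterm birth and low birth weight.

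It is also fair that the planned confidence intervals for the AUC would reveal some of the imprecision, though not the uncertainty of the cut-off itself. A minimum case count could be set in an analysis plan that is not at hand, but the protocol as written makes the commitment without any condition.

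**Conclusion.** The concern holds as a minor point. The protocol commits to a data-chosen cut-off for an outcome outside its objectives, with no condition on the number of cases. At an assumed prevalence of 0.5-2%, about 2 to 7 cases are expected before any loss to the exclusions. Perfect detection would then still be compatible with a true sensitivity as low as 16% (2 cases) or 59% (7 cases), before allowing for the choice of cut-off on the same infants. The optimism and spread in Step 5 depend on the assumed normal distributions and AUC values and are orders of magnitude only. The primary objective, the diagnostic accuracy of foot length for preterm birth and low birth weight, is not affected by this point. The use of all neonates as the denominator for precision is a separate and wider matter.

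**What to change.** In the Statistical analysis section, take one of two routes.

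1. Remove very low birth weight from the cut-off commitment.
2. Keep its ROC and cut-off analysis, labelled exploratory, and make it conditional on a minimum number of cases fixed before the data are seen. The minimum should be derived from the precision wanted. For example, a half-width of 10 points needs 1.96² × s(1−s)/0.10² cases, about 35 at a sensitivity of 90% and 81 at 70%.

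Under the first route, or if the minimum is not reached, report the number of infants under 1500 g, list their foot length, head circumference and MUAC, and give the proportion that fall below the low birth weight cut-off with an exact confidence interval. The Sample size section should also state the expected number of such infants with its assumption, and say that 342 is before the eligibility exclusions.

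The change is wording only. The cost is an exploratory cut-off that could not have been interpreted.
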